Assessment of the newborn infants’ response to maternal immunisation will focus on the nasal mucosa of the infants born to mothers enrolled in our study. Samples will be obtained on day of life 1 and at 6 weeks of age via a standardised, non-invasive and painless sampling procedure (Nasosorption), well-tolerated by newborn infants (and their parents) (37). These time points were chosen to coincide with infant health checks to reduce additional burden to parents. The neonatal nasal lining fluid absorption devices will be used to extract total proteins contrasting the infants’ developmental trajectory as a function of maternal immunisation status. The method of isolation of total proteins from the nasal lining fluids starts by thawing the devices on ice to preserve the integrity of the cells. Then, 300 ul of elution buffer (PBS (pH7.4) containing 0.05% (v/v) Tween20) is added. The synthetic absorptive matrix (SAM) is then removed from the nasosorption device using forceps by tearing it from the handle using sterile forceps. The SAM is then placed into a spinX column using a new pair of sterile forceps. After a centrifugation of the column and SAM at speed centrifugation(16,000 g) for 30 minutes at 4C, 260 ul of equate is reconstituted into a sterile tube and total proteins are quantified using Pierce BCA protein assay kit The protein identification and quantities will be assessed using Somascan, an untargeted Proteomics platform (Somalogic) capable of detecting more than 7000 proteins in less than 200ul of eluate (200ug/ml). In the testing assays performed by the study team, enough proteins were extracted from infant nasal lining devices and only a portion was used for proteomics analysis. The rest of the samples can be stored and used for targeted protein detection panels if interesting signals are detected from the initial untargeted analysis.

Our group and others have proven that when using this integrated multi-omic approach a sample size of 20 per group will suffice to identify robust (80% power) biological signatures related to pregnancy outcome with a two-sided significance criterion (alpha) of < 0.05. With this in mind, a sample size of 400 participants was chosen, assuming a background rate of PTB of 8%, it was estimated 32 women would delivery prematurely providing >20 per group.

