We will compare the immune trajectory of 20 unvaccinated women with 20 women who received either one of the two vaccines recommended in pregnancy, and 20 vaccinated with both vaccines. Recruitment started prior to the availability of COVID-19 vaccines but continued during the rollout of COVID-19 vaccines. Data on any vaccination during pregnancy is captured and will be taken into account in the analysis. Based on our previous work, we expect ~10 women in our cohort to choose to not be vaccinated at all, and approximately 50 women to be vaccinated with either influenza or pertussis alone. If we are unable to recruit 10 controls who have received no vaccination we intend to use women who are vaccinated late in pregnancy as a control over the time periods they remain “unvaccinated”. We will employ the same blood processing and data analysis pipeline summarised for Aim 1.

##### Aim 3

Samples will be obtained on day of life 1 and 6 weeks of life (day of recommended first follow up) via our highly standardised, non-invasive thus non-painful sampling procedure (Nasosorption), well-tolerated by newborn infants (and their parents) as described. We will process and analyse these 120 samples as described above contrasting the infants’ immune trajectory as a function of maternal immunisation status.

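### Aim 2 plans 20 unvaccinated women, expects about 10, and starts its fallback only below 10, so the stated size of the reference group is unlikely to be reached.

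*Protocol article*

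**What the plan says.** The Analysis plan section, under Aim 2, sets out three groups: "We will compare the immune trajectory of 20 unvaccinated women" against "20 women who received either one of the two vaccines recommended in pregnancy, and 20 vaccinated with both vaccines". The same paragraph then forecasts the supply: "we expect ~10 women in our cohort to choose to not be vaccinated at all". For women with only one of the two vaccines, its forecast is about 50. It adds a contingency that begins "If we are unable to recruit 10 controls who have received no vaccination". In that case the reference is to be "women who are vaccinated late in pregnancy as a control over the time periods they remain “unvaccinated".

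The only justification of group size is in the last paragraph of Sample collection, processing, storage and data generation: "a sample size of 20 per group will suffice to identify robust (80% power) biological signatures". That sentence concerns signatures of pregnancy outcome, at two-sided alpha 0.05. The cohort of 400 is derived there from preterm births alone. Under Aim 3, 120 infant samples are to be compared by maternal immunisation status.

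**The concern.** One paragraph gives three figures that do not fit together: a planned reference group of 20, a forecast of about 10, and a fallback threshold of 10. The threshold sits at the forecast and not at the planned size. With 10 to 19 never-vaccinated women, Aim 2 would therefore run below its stated size with no remedy in the text.

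The unvaccinated women are the reference for Aim 2 and, through their infants, for Aim 3. The effect of maternal immunisation on the immune trajectory is the study's central hypothesis. A reader who takes 20 per group at face value would credit these contrasts with about twice the reference group that the sponsor itself expects.

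**Working it through.** **Inputs from the article.** Cohort 400. Aim 2 groups 20, 20 and 20. About 10 never vaccinated and about 50 with one vaccine only. Fallback below 10. Preterm birth rate 8%. 20 per group for 80% power, two-sided alpha 0.05. 120 infant samples at two time points.

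**1. The article's own figures.** 400 × 0.08 = 32 preterm births, as stated. The binomial chance of at least 20 is 99.3%, so the cohort size supports Aim 1. The 80% power at 20 per group cannot be reproduced, because no effect size or standard deviation is given.

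**2. Chance of reaching the planned reference group.** The forecast rate is 10/400 = 2.5%. Let X be the number never vaccinated, X ~ Binomial(400, m/400), where m is the expected number. Since the forecast is approximate, m is varied; the values other than 10 are my assumption.

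| m | P(X ≥ 20) | P(10 ≤ X ≤ 19) | P(X ≤ 9) |
|---|---|---|---|
| 8 | 0.02% | 28% | 72% |
| 10 | 0.3% | 54% | 46% |
| 12 | 2.0% | 74% | 24% |
| 15 | 12% | 81% | 7% |

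The middle column is the gap: fewer than planned, and no fallback. At 2.5%, a cohort of 20 / 0.025 = 800 would be needed to expect 20.

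**3. What a smaller reference group does (illustration only).** Assume a two-group comparison of one mean and find the standardised effect d that gives exactly 80% power at 20 v 20.

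- Normal approximation: d = (1.960 + 0.842) × √(1/20 + 1/20) = 0.886. The noncentral t gives 0.909.
- Power at 10 v 20 for that effect: Φ(0.886/√(1/10 + 1/20) − 1.960) = Φ(0.328) = 63%. The t-test gives 62%.
- Power at 10 v 50, using all the expected single-vaccine women: Φ(0.886/√(1/10 + 1/50) − 1.960) = Φ(0.598) = 72%. The t-test gives 73%.

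Enlarging the vaccinated group recovers part of the loss, not all of it.

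**4. Aim 3.** 120 = (20 + 20 + 20) × 2, which matches the planned Aim 2 groups. With 10 never-vaccinated mothers and the other groups held at 20, the count is (10 + 20 + 20) × 2 = 100.

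**5. Reach of the fallback.** Late-vaccinated women can stand in only at blood samples taken before their dose. They cannot serve at later visits. They cannot serve for infants either, who are sampled on day 1 and at 6 weeks, after these mothers have been vaccinated.

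**The case against.** Several points on the other side have force.

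- **Power.** A reader might infer that Aim 2 is claimed to have 80% power and really has 62%. The article does not support this. Its power sentence is about pregnancy outcome, and Aim 2 has no power statement of its own. The planned pipeline (DESeq2 with a strict p-value filter, sPLS-DA, DIABLO) is also not a single-feature t-test. This objection stands: the 62% shows the direction and rough size of the loss and is not the study's power.
- **Impossible or unlikely.** A reader might infer that the forecast rules out 20. It does not: an expectation of 15 leaves a 12% chance. And at an expectation of 10 the fallback would be triggered 46% of the time.
- **A slip.** The 10 in the fallback sentence may be meant as 20. The article cannot settle this. If so, the gap from 10 to 19 closes, but the text still needs correcting, and visits after the dose and Aim 3 still rest on about 10.
- **Infant samples.** The 120 could be kept by enlarging the vaccinated groups. That is true, so 100 is conditional on those groups staying at 20.
- **Small groups.** The Rationale section says the approach works with groups of 20 or fewer. It gives no power for 10, so it does not resolve the mismatch.
- **Purpose.** This is an observational discovery study, and no conclusion from a null Aim 2 result is planned. That lowers the severity. It does not reconcile the figures.

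**Conclusion.** The inconsistency is real and needs no power argument: 20 planned, about 10 expected, and a fallback only below 10, with nothing elsewhere in the article to reconcile them. It is a conflict between stated figures, not a detail left to a fuller document.

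On the sponsor's forecast, reaching 20 is very unlikely (0.3%; 0.02% to 12% for expectations of 8 to 15), and about 54% of the probability lies where the plan falls short without a remedy. These figures assume independent choices at a constant rate across 400 women. The 20-per-group, 80% power statement should not be carried over to a contrast with about 10 controls. The drop to about 62% (about 73% at 10 v 50) rests on the assumed t-test and the back-solved effect.

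This should be fixed. It does not undermine Aim 1 or the cohort size of 400.

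**What to change.** 1. State the expected never-vaccinated group as about 10, and say that the 20-per-group, 80% power basis does not apply to that contrast. The illustrative 62% should not be written in as its replacement.
2. Set the fallback trigger at the planned size, fewer than 20. Late-vaccinated women contribute only visits before their dose. Say plainly that visits after the dose, and the infant comparison in Aim 3, still rest on about 10 never-vaccinated controls.
3. Restate the 120 samples of Aim 3 to match: about 100 if the vaccinated groups stay at 20 each, or the new group sizes if they are enlarged.
4. Add a sensitivity analysis of Aim 2 in never-vaccinated controls only.

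**Cost.** No extra women are needed, but the stated size is less favourable. Item 2 is more than a wording change: at an expectation of 10, a trigger of fewer than 20 would apply with probability 1 − 0.003 = 99.7%, so a mixed reference group becomes the norm at early visits. Item 4 checks how much that matters. If the sponsor prefers to keep late-vaccinated women as a last resort, the planned group should be restated as about 10 instead.

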**Figure 1 f1:**
[figure not shown]
Study Design (Created with BioRender.com).

Clinical data will be collected at baseline including established risk factors for PTB as well as past vaccination history. Pregnancy outcomes will be collected at birth. Venous blood (5mL) will be collected at each timepoint: 10-14 weeks, 20-22 weeks, 26-28 weeks, 34-36 weeks, and at birth (**Figure 2**).

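### On the plan's own forecast and fallback, Aim 3 has about 10 unexposed control infants, not the 20 its sample total implies, because late-vaccinated mothers cannot supply any

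*Protocol article*

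**What the plan says.** Under Analysis plan, Aim 2, the article sets three groups of 20: "We will compare the immune trajectory of 20 unvaccinated women with 20 women who received either one of the two vaccines recommended in pregnancy", and a third group of 20 who had both vaccines. The same paragraph forecasts the supply of controls: "we expect ~10 women in our cohort to choose to not be vaccinated at all". It then gives the fallback, which begins "If we are unable to recruit 10 controls who have received no vaccination" and continues "we intend to use women who are vaccinated late in pregnancy as a control over the time periods they remain" unvaccinated. The article gives no gestational week for late.

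Maternal blood is drawn at "10-14 weeks, 20-22 weeks, 26-28 weeks, 34-36 weeks, and at birth" (Recruitment and procedures, text after Figure 1). For infants, the section on sample collection says "Samples will be obtained on day of life 1 and at 6 weeks of age".

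Under Aim 3 the article fixes the amount of material, "We will process and analyse these 120 samples as described above", and the comparison, "contrasting the infants’ immune trajectory as a function of maternal immunisation status". It gives no rule for choosing Aim 3 controls other than the one for Aim 2.

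**The concern.** The fallback lends a woman to the control group for the part of pregnancy before her dose. That is a coherent idea for repeated maternal blood samples. It has no counterpart in infants: a woman vaccinated in pregnancy is vaccinated before she delivers, and both infant samples follow delivery. Her infant is exposed at both.

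Two things are at stake. First, the stated size of Aim 3 presupposes 20 control infants, which neither the forecast nor the fallback can deliver. Second, since no Aim 3 control rule is stated, an analyst who carries the Aim 2 group labels across to the infants would count exposed infants as controls and bias the comparison towards no effect. In Aim 2 there is a milder consequence: membership of the control series changes along the time axis and, once the fallback is used, the series ends before birth for the women it adds.

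**Working it through.** **Inputs.** Groups of 20, 20 and 20; about 10 never-vaccinated women expected; fallback if fewer than 10 (all Analysis plan, Aim 2). Cohort of 400 (Recruitment and procedures). Two infant time points (sample collection section). 120 infant samples (Analysis plan, Aim 3).

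**1. The plan's own figure.** (20 + 20 + 20) mothers × 2 infant time points = 120. This reproduces the stated total and indicates that Aim 3 uses the infants of the 60 Aim 2 women. That is an inference from the match; the article does not say so.

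**2. What a fallback woman can supply unexposed.** Compare the week of her dose with the sampling times:

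| Sample | Dose at week 29 or 33 | Dose after the 34-36 week draw |
|---|---|---|
| 10-14, 20-22 and 26-28 weeks | unexposed | unexposed |
| 34-36 weeks | exposed | unexposed |
| Birth | exposed | exposed |
| Infant, day 1 and 6 weeks | exposed | exposed |

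The weeks 29 and 33 are examples, since late is not defined. Whatever the week, she adds no unexposed birth sample and no unexposed infant sample.

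**3. Unexposed infants in Aim 3.** With u never-vaccinated mothers there are 2u unexposed infant samples. The total of 120 implies u = 20, giving 40 samples. The forecast of u = 10 gives 20. At u = 9 it is 18, and at u = 5 it is 10. Each fallback mother adds 0. With 10 to 19 never-vaccinated women the fallback is not triggered at all, yet the target of 20 is still missed.

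**4. How likely these cases are.** Treat the number of never-vaccinated women as binomial with n = 400 and p = (expected number)/400:

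| Expected number | P(fewer than 10) |
|---|---|
| 8 | 0.72 |
| 10 | 0.456 |
| 12 | 0.24 |

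At 10 expected, P(20 or more) = 0.003.

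**5. Size of the bias if exposed infants were counted as controls.** Let δ be the true effect, c the size of the control group, u the number truly unexposed, and λ the effect of a late dose as a fraction of δ. The expected contrast is δ × [1 − λ(c − u)/c].

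- λ = 1, u = 8, c = 10: 1 − 2/10 = 0.80 of δ.
- λ = 1, u = 8, c = 20: 1 − 12/20 = 0.40 of δ.
- λ = 0.5 (an assumption): 0.90 and 0.70 of δ for the same two cases.

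**6. Is a small clean group better than a filled one?** The article gives no effect size, so this is illustration only. Assume a standardised difference of 0.886, which gives 80% power at 20 v 20 with two-sided α = 0.05, and assume λ = 1. With u = 9:

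- controls filled to 20 with exposed infants: power 24%;
- controls filled to 10: 54%;
- only the 9 unexposed infants against 20: 60%.

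With u = 10 and no filling, power is 63%. Under these assumptions adding exposed infants lowers power despite the larger group.

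**The case against.** The strongest reply is that the fallback stands under Aim 2 and is limited to the time a woman is still unvaccinated. Read literally, it admits no infant, because no infant sample falls in that time; and an Aim 3 comparison by maternal immunisation status would place a late-vaccinated mother's infant with the exposed. This stands. A reader might infer that the plan does put exposed infants among the controls, but the documents do not say so. What remains is that the total of 120 matches 20 per group and that no Aim 3 control rule is given. Detail may sit in the full protocol, but the mismatch between the target of 20, the forecast of about 10 and the total of 120 is in the article itself.

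Other stronger readings also fail:

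- **No unexposed sample late in pregnancy.** Too absolute: a woman vaccinated after her 34-36 week draw gives an unexposed sample there. Only the birth sample is always exposed. The article already limits these women to their unvaccinated periods, so it does not mislabel their later blood samples.
- **A loss of 60% of the effect.** This needs filling to 20 and a late dose as effective as an earlier one. The article names 10 as the trigger, gives no number to fill to, and says nothing on the effect of a late dose.
- **The total must fall to 100.** (10 + 20 + 20) × 2 = 100 holds only if nobody else is sampled. About 50 women are expected to have one vaccine alone, so 120 remains reachable with unequal groups.
- **Loss of early preterm births as a special flaw of the fallback.** Anyone vaccinated in pregnancy had to remain pregnant until the dose, so the vaccinated groups share this selection to a degree set by dose timing. The Aim 2 outcome is the immune trajectory, not preterm birth.

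**Conclusion.** The point holds in limited form. The Aim 3 total implies 20 unexposed infants, while the plan's own forecast supports about 10, and its fallback cannot add any. That follows from the sampling schedule and needs no statistical assumption beyond reading 120 as 60 × 2.

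The bias is conditional: it arises only if infants of late-vaccinated mothers are counted as controls, which the article neither states nor rules out. Its direction would then be towards no effect. Its size depends on how many are added and on the effect of a late dose, and the 80% and 40% figures are examples under equal effects. The chance of needing the fallback, about 46%, takes the forecast as exactly 10 of 400; a plausible range is 24% to 72%.

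For Aim 2 the conclusion is narrower still: at birth only never-vaccinated women can serve as controls, and the control count at 34-36 weeks is unknown until late is defined.

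**What to change.** - State that the fallback applies to Aim 2 maternal samples only.
- Define late against the visit schedule, and report the number of controls at each visit, with only never-vaccinated women as controls at birth.
- In Aim 3, take as unexposed only infants of mothers never vaccinated in pregnancy, and analyse infants of late-vaccinated mothers as exposed.
- Restate the expected Aim 3 control group as about 10 infants (20 samples), and restate how the 120 samples divide. The total may stay at 120 with unequal groups.

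The cost is wording and a smaller stated control group. No added recruitment or sampling is needed. The smaller group means less power than 20 per group would give (63% rather than 80% at 10 v 20 in the illustration above), and the article should acknowledge this for Aim 3.

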#### Analysis plan

##### Aim 1

We will compare the immune trajectory of all women with a preterm birth (estimated to be 8% of our total sample size) with a matched control group of women who deliver at term. We will not be performing multiomics on all participants recruited. To assess the immune trajectory in relation to pregnancy outcome longitudinally over time we will identify features both in the univariate and multivariate space. For univariate analysis, differentially expressed (DE) genes, proteins, or metabolites will be identified using DESeq2 v1.26. Correction for multiple comparisons will be done to control for false discoveries, filtering results based on a highly conservative p-value for significance (<0.001). Sparse Partial Least Squares - Discriminant Analysis (sPLS-DA) will be used to identify discriminatory features that co-vary with each other. Given the user-defined sparsity feature of sPLS-DA, and with the readout being classification accuracy, no p-value adjustment is necessary for this method. To assess the data in their biological context, i.e. integrated multi-omics, we will use two complementary integration strategies. *NetworkAnalyst* is based on known protein-protein interaction (PPI) networks and *DIABLO*, part of the *mixOmics* framework, a data-driven multi-omic integration approach. Given that *DIABLO* selects features that allow maximum class distinction (i.e. accurate classification of pregnancy outcome), this approach will also identify the earliest point during pregnancy that can accurately predict an adverse birth outcome. Finally, time course analyses that generate smoothing splines allow identification of groups of features that follow the same trajectory in a multivariate space. The *DynOmics* toolbox is an extension of the *mixOmics* toolbox used for multi-omic datasets built to identify these dynamic longitudinal changes in biological systems, while integrating multi-omic data.

##### Aim 2

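### Classification accuracy has no fixed chance level when class sizes differ, as the plan's own numbers imply for Aim 2 and as early delivery may cause at 34-36 weeks in Aim 1

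*Protocol article*

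**What the plan says.** All of this is in the protocol article. Under Analysis plan, Aim 1, the sPLS-DA step is justified as follows: "with the readout being classification accuracy, no p-value adjustment is necessary for this method". The same section then says of DIABLO that "this approach will also identify the earliest point during pregnancy that can accurately predict an adverse birth outcome". Accuracy is therefore both the evidence for a signature and, in effect, the scale on which visits are compared. No chance level, per-class rate or correction for class size is given.

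Aim 1 sets all preterm births against term controls matched to them, without a matching ratio. It gives no rule for the controls of women who have already delivered when a later sample falls due. Recruitment and procedures schedules blood at 10-14, 20-22, 26-28 and 34-36 weeks and at birth.

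Aim 2 inherits the pipeline: "We will employ the same blood processing and data analysis pipeline summarised for Aim 1". Its design is "20 unvaccinated women with 20 women who received either one of the two vaccines recommended in pregnancy, and 20 vaccinated with both vaccines". The same paragraph, however, states that "we expect ~10 women in our cohort to choose to not be vaccinated at all", and its fallback reads: "If we are unable to recruit 10 controls who have received no vaccination we intend to use women who are vaccinated late in pregnancy". Those late-vaccinated women count as controls only for the part of pregnancy before their vaccination.

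**The concern.** Overall accuracy weights every woman equally, so a rule that always names the largest class scores that class's share of the sample. When classes are equal this is the familiar 50% or 33%. When they are not, the reference moves, and a given accuracy can no longer be read at face value or set against the accuracy from another visit or contrast.

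Two features of this plan make the classes unequal. In Aim 2 the unvaccinated group, on which the aim depends, is expected to reach about half its planned size. In Aim 1 the preterm group can shrink before the last antenatal draw because its members have given birth. This is a separate issue from overfitting: cross-validation gives an honest estimate of accuracy but does not change what accuracy measures. At stake is whether a reported accuracy in Aim 2, or a change in accuracy between visits in Aim 1, can be told apart from a change in class mix.

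**Working it through.** **Inputs from the article.** 400 women and 8% preterm birth; Aim 2 groups of 20/20/20; about 10 women expected unvaccinated; fallback only below 10 controls; 120 infant samples in Aim 3.

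**The plan's own figures.** 400 × 0.08 = 32 preterm births, as stated. 60 mothers × 2 infant visits = 120 samples, which agrees with 20/20/20. The article gives no chance level for accuracy, so there is none to reproduce.

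**Formula.** No-information accuracy = largest class ÷ total. Balanced accuracy = mean of the per-class proportions correct. For the same always-largest rule it is 1 ÷ number of classes, whatever the sizes: (0 + 1)/2 = 50% for two classes and (0 + 0 + 1)/3 = 33.3% for three. The balanced error rate is one minus this.

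**Aim 2.**

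| Contrast | As planned | With 10 unvaccinated |
|---|---|---|
| Three classes | 20/60 = 33.3% | 20/50 = 40.0% |
| Unvaccinated v one vaccinated group | 20/40 = 50.0% | 20/30 = 66.7% |

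The fallback does not restore 20 controls, because it is triggered only below 10. If it is used, the control count also falls from visit to visit as those women are vaccinated.

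**Aim 1, 34-36 week draw.** Two assumptions are needed that the article does not supply: 1:1 matching (32 controls), and a share f of the 32 preterm women delivered before the draw. If controls stay in, the score is 32 ÷ (32 + 32(1 − f)) = 1 ÷ (2 − f).

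| f | 0 | 10% | 20% | 30% | 40% | 50% |
|---|---|---|---|---|---|---|
| Score | 50.0% | 52.6% | 55.6% | 58.8% | 62.5% | 66.7% |

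If each control leaves with its case, the score is 50% for every f. At the birth sample all women can contribute again, and it returns to 50%.

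**What a fitted classifier does on noise.** Simulation with no signal: one-component sparse PLS-DA, 1,000 noise features with 30 kept, 5-fold cross-validation, 400 runs per setting. The two accuracy figures are for the maximum-distance and centroid rules.

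| Classes | Always-largest score | Accuracy on noise |
|---|---|---|
| 32 v 32 | 50.0% | 49.8% / 49.8% |
| 22 v 32 | 59.3% | 52.5% / 51.8% |
| 16 v 32 | 66.7% | 60.1% / 58.4% |
| 10 v 20 | 66.7% | 59.6% / 58.4% |

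Balanced accuracy stayed between 49.5% and 50.9% in every setting tried. The inflation is thus real after cross-validation, but smaller than the always-largest score suggests.

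**The case against.** The strongest reply has four parts.

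- **Equal groups are the plan.** Aim 2 specifies 20/20/20, and because multi-omics will not be run on everyone, the number of vaccinated women profiled is a choice. Equal groups of 10 are therefore possible. That is true, but the article does not say the vaccinated groups would be cut to match, and its fallback accepts 10 controls against groups of 20.
- **The Aim 1 drift rests on unstated quantities.** Matching ratio and delivery weeks are not given. If few preterm births precede 26-28 weeks (also an assumption), the effect is essentially confined to one of five draws, and keeping matched sets together removes it. This stands, which is why only a conditional range is given.
- **The bias does not favour a false early claim.** The stated goal is the earliest predictive visit, and inflation at the last antenatal draw works the other way. This stands too. What remains is that accuracies at different visits may not be on one scale.
- **The article is condensed.** It does not say whether accuracy is overall or balanced, and the full plan may. But the article names the metric and relies on it to dispense with p-value adjustment, so the choice is open to comment as written.

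A reader might infer that an uninformative rule scores 80% in Aim 2. That needs both vaccinated groups pooled against 10 unvaccinated women (40/50), and the article states three groups, not that contrast. A reader might also infer that accuracy will rise late in pregnancy through attrition alone. The article gives no birth-week distribution from which to conclude this, and the noise accuracy rises less than the always-largest score. Nor is it shown that feature selection would favour rules that ignore the small class: the article describes DIABLO as selecting for class distinction.

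**Conclusion.** The concern holds in a limited form. Accuracy is the stated readout, it carries over to Aim 2, and its no-information value depends on class sizes that the article's own figures make unequal. For Aim 2 at 10/20/20 the reference is 40% rather than 33% across three classes and 67% rather than 50% for unvaccinated against one vaccinated group. These values need only the expected 10 controls and vaccinated groups of 20. For Aim 1 the reference at 34-36 weeks lies between 50% and 67% if matching is 1:1, 0-50% of preterm women have delivered, and their controls are kept. It is 50% if matched sets stay together. A false finding does not follow from this. The consequence is that accuracies from different contrasts or visits cannot safely be compared without an adjusted scale. The remedy is cheap enough that the plan should adopt it.

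**What to change.** In Analysis plan, Aim 1, where the article has "with the readout being classification accuracy", substitute the balanced error rate (the mean of the class-specific error rates), or AUC for two-class contrasts, and state that it is used both for tuning and for reporting sPLS-DA and DIABLO in all aims. Add that each visit will be reported with its class counts and an interval for this measure, that visits will be compared only on this scale, and that matched case-control sets will be kept together at each visit.

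Reporting plain accuracy beside its majority-class or permutation reference would make single results readable. It would leave tuning on the unadjusted metric and visits on different scales, so it is second best.

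The cost is a few sentences and a software option, with no new samples. Headline figures will be lower, and intervals wider for the small class. Keeping sets together also sets aside, at 34-36 weeks, the controls of women already delivered: at f = 30%, about 32 × 0.7 = 22 pairs remain of 32.
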